### Data collection methods

#### Effectiveness data

Routinely collected medical record data (including hospital coded data) incident management system data and quality audit reporting system data will be extracted for participating wards in the specified timeframes. These data are collected by the health facilities using routine methods, as required by hospital accreditation agencies. Data will be extracted for 5 months prior to the first cluster’s intervention implementation and for nineteen months following this. Primary outcome data will not be collected during the wash-in period. Figure 2 provides an overview of the study periods.

#### Implementation data

Implementation level data will be collected pre-implementation and post-implementation to measure implementation outcomes and determinants. This will be collected via:

Staff pre-implementation and post-implementation anonymous surveys.Patient and patient family member pre-implementation and post-implementation anonymous surveys.Staff and patient/family interviews.Ward-specific pre-implementation and post-implementation audits (including observation and medical record review).Study records/fieldwork notes.

The staff pre-implementation and post-implementation surveys and interview guides (included in online supplemental material 4) have been piloted in the feasibility study that informed this trial.^21^ Changes to these surveys and interview guides were based on feedback from staff participants and study personnel in the pilot study (informally and formally through qualitative interviews). Additional questions have been added relevant to some implementation determinants and staff professional fulfilment, including from two validated survey tools: safety attitudes questionnaire^50^ and the professional fulfilment index.^51^ Implementation questions in staff and patient/family surveys are based on a recommended minimum dataset of indicators for implementation evaluation. These need to be specific to the intervention being implemented and thus cannot come directly from a validated tool. We have, however, been guided by survey and interview guide development literature.^52 53^ Free-text survey questions and specific questions in the interview guide intend to provide data informing the effectiveness and suitability of the individual implementation strategies and suggested future tailoring of these (see online supplemental material 4 for surveys and interview guides).

Ward-by-ward results of the pre-implementation survey data, pre-implementation ward audit data and pre-implementation incident management system data will inform an individual ward needs analysis and subsequent tailoring of the implementation strategy to meet these needs.

### Cost-effectiveness data collection methods

#### Health utilisation and intervention and implementation cost data

Intervention and implementation cost data for the economic evaluation will be collected from trial-based records for the trial duration. Healthcare utilisation during the trial duration will be collected from routinely collected coded hospital data. Healthcare utilisation will be valued using local or national costs as appropriate and all costs will be valued in Australian dollars. Discounting will not be applied, as the time horizon will be limited to the trial duration.

### Harms

Unexpected and related serious adverse events (URSAEs) perceived to be related to the trial intervention will be reported by the Nurse Unit Manager of the participating ward Manager (who will be educated about this procedure at the time of consent) to a member of the study team. URSAEs will be reported to the independent Data Safety Monitoring Board, as well as to the approving Human Research Ethics Committee (HREC), and amendments to the protocol will be considered as necessary.

### Statistical analysis

#### Effectiveness analysis

Statistical analysis will compare the rate of falls (primary outcome) and injurious falls and unwitnessed falls (secondary outcomes) between intervention and control time periods using a ward/time-period approach. The distribution of the falls will be examined as part of the model building, as these data are commonly skewed. If indicated, we will use negative binomial regression to estimate the difference in the rate of falls, expressed as an incidence rate ratio and 95% CI. Secondary analyses may use patient-level data and rates of falls per occupied bed days and will be clustered within ‘wards’. Secondary analyses using causal modelling may also be conducted to establish intervention effects in wards with greater uptake.^54^ Additionally, secondary analyses adjusting for covariates such as patient complexity may be undertaken. All analyses will be conducted while masked to group allocation and will use an intention-to-treat approach. Analyses will use Stata and R. Sensitivity analyses to adjust for any potential risks of bias that arise during the study may be conducted. The detailed statistical plan will be publicly available prior to the analysis commencing.

#### Survey analysis

All returned surveys that have at least one response will be included for analysis. Descriptive statistics (means, SD, change, counts and percentages) will be used to analyse survey data.

Quantitative implementation analysis of survey data will involve numerical description of quantitative implementation measures, presented as percentages or means and exploration with relative risks. Changes from pre-delivery to post-delivery of implementation strategies in self-reported staff and patient/family surveys will be evaluated using paired-sample t-tests. Univariate correlations will explore changes in these measures.

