**Figure 2 F2:**
[figure not shown]
Study flowchart. EOI, Expression of Interest.

Staff from nursing, medical, physiotherapy, occupational therapy, dietetics, speech pathology, social work, pharmacy, podiatry, orthotics, diversional therapy, administration and environmental services disciplines working on the participating wards, and inpatients and their family members on the participating wards, will be invited to complete pre-implementation and post-implementation surveys. Given the high turnover of inpatients and staff in many wards and to keep survey responses anonymous, participants in the pre-implementation and post-implementation surveys do not need to be the same. Staff, inpatients and their families will also be invited to participate in post-implementation interviews.

Inclusion and exclusion criteria for the various aspects of the study are provided in table 1.

**Table 1 T1:** Inclusion and exclusion criteria for components of the study

Participants	Inclusion criteria	Exclusion criteria
Hospital wards	Inpatient hospital wards at participating hospitals. Support for nursing and other involved discipline executives to participate in the programme.	Emergency departments. Intensive care units. Paediatric and neonatal wards. Wards currently participating in another research trial with patient falls as a listed outcome. Outpatient settings.
Staff pre-implementation survey participants	Employed by participating hospitals. Work in nursing, medical, physiotherapy, occupational therapy, dietetics, speech pathology, social work, pharmacy, podiatry, orthotics, diversional therapy, administrative or environmental services teams on a ward enrolled to participate in the intervention.	Nil.
Staff post-implementation survey and interview participants	Employed by participating hospitals. Work in nursing, medical, physiotherapy, occupational therapy, dietetics, speech pathology, social work, pharmacy, podiatry, orthotics, diversional therapy, administrative or environmental services teams on a ward that participated in the intervention.	Has worked on the participating ward for <1 week.

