### Sample size

Our design will provide 80% power to detect a 25% lower fall rate for intervention compared with the control phases (IRR=0.75), using a significant level of α at 0.05. Sample size calculations used the method described by Hemming and Taljaard^37^ with coefficients from previous studies^6 8^ and data from our partner organisations. To determine the appropriate sample size for the complete stepped-wedge design, we used the Stata function “steppedwedge”^38^ following the Hussey and Hughes approach,^39^ and conservatively assumed an intra-cluster correlation of 0.007.

The primary outcome is the falls rate (falls per 1000 bed days). Based on partner organisations’ monitoring data, we determined that 30 beds per ward for three steps and four clusters per sequence will result in 14 400 bed days in four wards for 120 days (3 months), providing >80% power.^38^,^40^ An estimated 5808 patients are expected to be admitted to the study wards during the study period.

Sample size calculations for the pre-implementation and post-implementation surveys were based on paired t-tests using survey data from our feasibility study. Assuming a SD of 0.8, the proposed sample sizes will provide 80% power to detect a mean change of 0.5 points on the Likert scale, as measured by survey questions.

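### Survey sample size and analysis use paired t-tests, but the surveys are anonymous, respondents may differ between waves, and no pairing unit is given

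*Protocol article*

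**What the plan says.** Two parts of the protocol article fix the method. Under Sample size: "Sample size calculations for the pre-implementation and post-implementation surveys were based on paired t-tests using survey data from our feasibility study". The spread is given as "Assuming a SD of 0.8", and the claim made on that basis is that "the proposed sample sizes will provide 80% power to detect a mean change of 0.5 points on the Likert scale". Under Survey analysis: "Changes from pre-delivery to post-delivery of implementation strategies in self-reported staff and patient/family surveys will be evaluated using paired-sample t-tests". That section also plans univariate correlations to explore the changes, and it admits every returned survey with one or more answers.

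Two other parts fix the design of the surveys. Study design, randomisation, setting and participants (after the Figure 2 caption) says that "participants in the pre-implementation and post-implementation surveys do not need to be the same"; the reasons offered are turnover among patients and staff, and anonymity. Implementation data lists "Staff pre-implementation and post-implementation anonymous surveys" and describes the patient and family surveys as anonymous too.

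Table 1 is consistent with that. Post-implementation staff respondents are excluded only if they have been on the ward for less than a week, so staff who joined after the first wave are eligible. Patient respondents need only be current inpatients, or their family or carers, at the time of the survey.

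**The concern.** A paired t-test works on within-unit differences. It needs a pre score and a post score that belong to the same unit and can be matched. The surveys as described supply neither for individuals: the two sets of respondents may differ, and anonymity prevents matching those who happen to answer twice. With a 17-week intensive support period between the waves, few patients could answer both.

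This affects the survey-based implementation outcomes and determinants in Table 3, which carry much of the implementation half of a hybrid trial, and staff professional fulfilment, a secondary effectiveness outcome measured by staff survey and interviews. The power statement for these comparisons depends on a pairing that the design does not provide. Because the article names the test in both the sample size and the analysis, this is not a detail left to the later statistical plan: a plan that followed the article would inherit the conflict.

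**Working it through.** **Inputs**
- Mean change 0.5, SD 0.8, power 80%, paired t-test (Sample size).
- Alpha: "using a significant level of α at 0.05" is stated for the primary outcome only. Two-sided 0.05 is assumed here for the surveys.
- Survey n: not given; the article refers only to the proposed sizes.
- Meaning of the SD of 0.8 (single score or within-person change): not stated.

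**The plan's own figure.** The 80% cannot be reproduced without an n, so I solve for the n that its inputs imply. Taking 0.8 as the SD of change:
- Normal approximation: n = ((1.960 + 0.842) × 0.8 / 0.5)² = (2.802 × 1.6)² = 20.1, so 21 pairs.
- Noncentral t: n = 22.1, so 23 pairs (power at 23 is 82%).

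**Two independent waves, 0.8 as the SD of a single score**
- Normal approximation: n = 2 × 20.1 = 40.2, so 41 per wave.
- t-test: 41.2, so 42 per wave.
- Power with 23 per wave: about 55%.

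Under this reading the paired requirement itself depends on the pre/post correlation ρ, since the SD of change is 0.8 × √(2(1 − ρ)). For ρ = 0, 0.3, 0.5 and 0.7 it is 43, 31, 23 and 15 pairs. The 23 is therefore not a figure that can be attributed to the plan.

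**Two independent waves, 0.8 as the SD of change.** The single-score SD is then 0.8 / √(2(1 − ρ)), with ρ assumed:

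| Assumed ρ | Single-score SD | n per wave for 80% (t-test) | Power at 23 per wave |
|---|---|---|---|
| 0 | 0.57 | 22 | 83% |
| 0.3 | 0.68 | 30 | 69% |
| 0.5 | 0.80 | 42 | 55% |
| 0.7 | 1.03 | 68 | 36% |

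**Clustering.** All these figures are before any allowance for respondents sharing a ward. The article gives no survey intra-cluster correlation, so none is applied.

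**Analysis set.** Including every returned survey fits two cross-sections. A paired test on matched respondents would have to discard every unmatched survey.

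**The case against.** The strongest reply is that the text says respondents need not be the same, not that they will all differ. Some staff will probably answer both waves, and an anonymous self-generated code could link them; the survey instruments are in a supplement that is not shown. This stands as a possibility, but the article describes no such code, and it would not help with patients.

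The second reply is ward-level pairing. Implementation data speaks of ward-by-ward results of the pre-implementation surveys, so those surveys can be attributed to wards. If the later ones can too, a paired test on 12 ward means is computable, as are correlations of ward-level changes. A reader might infer that no paired analysis of any kind is possible; the documents do not support that. They also do not say that ward means are the intended unit. With an SD of 0.8 for the change in ward means, 12 pairs would give about 51% power, but the article does not give that SD.

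The third reply concerns power. A reader might infer that true power is 55%, or that the stated 80% is not achieved. Neither is established: 23 is a back-calculation, the planned n is unknown, and if 0.8 is the SD of change with ρ near 0, 23 per wave would still give about 83%. For the same reason 42 per wave is not a requirement that can be prescribed. This objection stands in full.

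Finally, the primary falls analysis and the other routine-data outcomes do not use the surveys, and the survey analysis is also descriptive. That limits the reach of the point without removing it.

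**Conclusion.** The point holds: the stated method conflicts with the stated survey design. As the article describes the surveys, individuals have no linked pre and post scores, so an individual-level paired t-test and correlations of individual change cannot be run. The paired basis for the 80% survey power does not match the data that will be collected.

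The size of the power loss cannot be stated. Under the assumptions shown, independent waves would need between about 22 and 68 respondents each, against 23 pairs, depending on what the SD of 0.8 means and on an assumed correlation. The conclusion about the conflict depends on none of these numbers. It rests on there being no linkage or pairing unit in the article; if one exists elsewhere, stating it would answer the point for the linked units only.

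**What to change.** - Replace the paired t-test with a comparison of two independent cross-sections: for example a linear or ordinal mixed model with a fixed pre/post term and ward random effects, fitted separately for staff and for patients/family. If some staff answer twice without being linked, treating the waves as independent will usually err on the cautious side.
- Keep correlations of changes only at ward level, and say so.
- Restate the survey power on the same basis: give the planned n per wave for each survey, say whether 0.8 is the SD of a single score or of the change, state alpha, and state the allowance made for wards.
- If a linking code or ward-level pairing was in fact intended, name it and define which surveys enter that analysis.

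The cost is wording in the protocol and the statistical plan, and possibly a less favourable power statement. Data collection does not change. The choice should be settled before the analysis begins, since anonymous surveys cannot be linked afterwards.

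### Survey changes are tested and powered with paired t-tests that make no allowance for ward, although respondents sit in 12 wards with ward-specific programmes

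*Protocol article*

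**What the plan says.** The Survey analysis section names the test for change between the two survey waves: "Changes from pre-delivery to post-delivery of implementation strategies in self-reported staff and patient/family surveys will be evaluated using paired-sample t-tests". The Sample size section uses the same basis: "Sample size calculations for the pre-implementation and post-implementation surveys were based on paired t-tests using survey data from our feasibility study". It continues "Assuming a SD of 0.8", and then says that "the proposed sample sizes will provide 80% power to detect a mean change of 0.5 points on the Likert scale". The number of surveys is not given, and neither section mentions ward, an ICC or a design effect.

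Clustering is recognised elsewhere. The falls sample size uses an ICC of 0.007. In the Effectiveness analysis section the falls comparison works by ward and time period, and the possible secondary analyses may use patient-level data and "rates of falls per occupied bed days and will be clustered within" wards.

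Two further statements bear on the point. Under Implementation data, ward-by-ward survey, audit and incident results "will inform an individual ward needs analysis and subsequent tailoring of the implementation strategy to meet these needs". Under Study design, randomisation, setting and participants, the surveys are anonymous and the people answering before and after need not be the same.

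**The concern.** Staff on one ward share managers, workload and culture, and its patients share staff and surroundings, so their answers are likely to be correlated. Stable differences between wards largely cancel when the same wards are compared before and after. What does not cancel is variation between wards in the change itself. This trial makes such variation likely: each ward designs its own interventions, receives its own tailored support and crosses over at one of three times.

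A t-test that treats individuals as independent omits this component. Where it is appreciable, standard errors are too small, intervals too narrow, and changes are declared more often than the nominal 5%. The results affected are staff professional fulfilment, which is a listed secondary effectiveness outcome, and the many survey-based rows of Table 3. In a hybrid effectiveness-implementation trial these support the claims about implementation.

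**Working it through.** **Inputs from the protocol:** 12 wards; SD 0.8; change 0.5; power 80%; paired t-test. Alpha of 0.05 is stated for the falls outcome and is assumed here, two-sided, for the surveys. Respondents per ward per wave (m), the survey ICC, and the share of ward variance common to both waves (c) are not given, so they are varied as assumptions.

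**Step 1: what the stated 80% implies.** The figure cannot be reproduced directly because the survey n is missing, but the n it implies can be found (noncentral t, no clustering).
- SD 0.8 as the SD of paired differences: 22 pairs give 79.8% and 23 pairs give 81.7%, so 23 pairs (about 2 per ward).
- SD 0.8 as the SD of single scores, waves unlinked: 41 per wave give 79.8% and 42 give 80.8%, so 42 per wave (42/12 = 3.5 per ward).
- Twelve ward-mean pairs with SD 0.8: 50.6%.

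The stated power therefore fits independent individuals and not 12 ward means, unless the SD of 0.8 means something else at ward level.

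**Step 2: variance of the change.** For unlinked waves in the same wards, the true variance of the difference divided by the variance that a pooled t-test assumes is

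ratio = 1 + (m − 1) × ICC − m × ICC × c.

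Type I error of the nominal 5% test = 2 × [1 − Φ(1.96/√ratio)].

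| m | ICC | c | ratio | type I error |
|---|---|---|---|---|
| 3.5 | 0.05 | 0.5 | 1 + 0.125 − 0.0875 = 1.04 | 5.4% |
| 3.5 | 0.10 | 0.5 | 1 + 0.25 − 0.175 = 1.08 | 5.9% |
| 3.5 | 0.05 | 0.8 | 1 + 0.125 − 0.14 = 0.99 | 4.8% |
| 3.5 | 0.10 | 0.8 | 1 + 0.25 − 0.28 = 0.97 | 4.7% |
| 4 | 0.05 | 0.5 | 1 + 0.15 − 0.10 = 1.05 | 5.6% |
| 4 | 0.10 | 0.5 | 1 + 0.30 − 0.20 = 1.10 | 6.2% |
| 10 | 0.05 | 0.5 | 1 + 0.45 − 0.25 = 1.20 | 7.4% |
| 20 | 0.05 | 0.5 | 1 + 0.95 − 0.50 = 1.45 | 10.4% |
| 20 | 0.10 | 0.5 | 1 + 1.90 − 1.00 = 1.90 | 15.5% |
| 20 | 0.05 | 0.8 | 1 + 0.95 − 0.80 = 1.15 | 6.8% |

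Simulation with 12 wards (5,000 data sets per setting, c = 0.5) gave 10.3% and 15.9% for the pooled test at m = 20 with ICC 0.05 and 0.10. A paired test on the 12 ward means stayed at about 5% throughout.

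**Step 3: effect on the stated power.** Starting from exactly 80%, power = Φ(2.80/√ratio − 1.96). At the implied 3.5 per ward and c = 0.5, this is 78.5% (ICC 0.05) and 77.0% (ICC 0.10). At c = 0.8 it is 80.5% and 81.1%, so nothing is lost. If pairs could be linked, 23 pairs would have 79.8% or 77.9% power for an ICC of the change of 0.05 or 0.10, against 81.7% without clustering.

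**The case against.** The strongest reply is that pooling is inferred. No unit of analysis is named, anonymous surveys cannot be paired by person, and pairing by ward remains possible, so the authors may intend it. This stands as a caution. Against it, the protocol describes no ward-level pairing, and its power inputs do not fit 12 ward means at the stated SD.

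A second reply is that the effect is negligible at the only survey size the inputs imply, and a pooled test could even be slightly conservative when ward differences are stable. This also stands, for that size. But all surveys with at least one response are to be analysed and many disciplines are invited on each ward, so returns may be well above 3.5 per ward, and the inflation grows with returns.

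Third, these are secondary and implementation outcomes, largely handled descriptively, and a detailed statistical plan is promised. That limits the weight. It does not remove the point, because the test and its power basis are stated, not left open.

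Two stronger readings are tempting and not supported.
- A reader might apply the ratios of 1.45 and 1.90 to the stated 80% and conclude that power drops to about 64% or 53%. Those ratios belong to 20 per ward, that is 240 per wave, where SD 0.8 and change 0.5 still give more than 99% power after the inflation. The 80% belongs to about 42 per wave.
- A reader might say that the effective sample is only 12. Twelve is the number of clusters; 240 per wave divided by 1.45 or 1.90 is still about 166 or 126.

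**Conclusion.** The point holds as a moderate one. The protocol fixes a survey test, and a power basis, that make no allowance for ward in a programme designed to differ by ward. With half of the ward variance shared between waves and an ICC of 0.05 to 0.10, all assumed, a pooled individual-level test has a type I error of about 5-6% at 3.5-4 respondents per ward per wave and about 10-16% at 20. If more of the ward variance is stable, or few surveys come back, the effect is small. The loss of power at the implied sample size is about 0-3 points for unlinked waves, so the documents do not show that the stated survey power is materially overstated by clustering. It is likewise not established that changes will be declared too often: that depends on the survey n, the ICC and the between-wave ward correlation, none of which is given. The primary falls analysis is untouched.

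**What to change.** In Survey analysis, replace the paired t-test by one of two analyses:
- a paired test of the 12 ward mean changes (11 degrees of freedom); or
- a mixed model with wave as fixed effect, ward and ward-by-wave random effects, and small-sample degrees of freedom.

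Both also work with anonymous respondents who cannot be linked, which the paired test on individuals does not. Report survey means and percentages with intervals that allow for ward.

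In Sample size, give the survey n, say whether 0.8 is the SD of single scores or of differences, and restate power for the chosen analysis over a range of ICC and between-wave ward correlation.

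The cost is analysis wording and somewhat wider intervals; no new data are needed. As a guide to the cost, with c = 0.5 and ICC 0.05 to 0.10, the 11-df ward-level test has about 71-73% power at 42 per wave. It has about 83-85% at 5 per ward (60 per wave) and 96-98% at 10 per ward (120 per wave).
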